**ABSTRACT**

**Objectives:** To examine the efficacy of Fitbit facilitated walking intervention in addition to usual care in people with low back pain who have been categorized as being at medium or high risk of chronicity in reducing disability and pain.

**Design:** Randomised controlled trial**.**

**Setting:** Physiotherapy outpatient departments of public and private hospitals or private physiotherapy practices in Sydney, Australia.

**Participants:** This study will recruit participants who are aged 18 years or over, have been diagnosed with non-specific low back pain with medium or high risk of chronicity and classified as physically inactive.

**Interventions:** Participants will be randomised into two groups: usual physiotherapy care (n=34) and usual physiotherapy care plus Fitbit facilitated walking intervention program (n=34). The treatment duration will be 8 weeks. The outcomes will be assessed at baseline, post-intervention and 26 weeks post randomisation follow-up.

**Main outcome measures:** The primary outcomes for this study are disability and pain. The secondary outcomes include physical activity level and walking steps, depression, fear of movement and pain catastrophising,

**Discussion:** The results of this study will provide empirical evidence on the efficacy of Fitbit facilitated walking intervention program, when added to usual care, in a clinical setting for improving disability and pain, and other clinical outcomes in people with low back pain.

**Trial registration:**

**Keywords:** Low back pain, Physical activity, Walking, Fitbit, Randomised controlled trial, Protocol.

**INTRODUCTION**

Low back pain (LBP) is one of the most common conditions presenting to health professional and is a major health problem globally.^1^ The lifetime prevalence of LBP is reported to be as high as 84% worldwide.^2^ Around 23% of the population has chronic non-specific LBP.^3, 4^ The risk of developing chronic LBP has been associated with various individual, psychosocial (e.g. depression, fear of movement and pain catastrophizing) and occupational factors ^5-11^; leading to high levels of disability and imposing high direct and indirect costs to the individual and the community.^1-3, 6, 8-10, 12^

Several studies have shown the association of catastrophizing with depression and fear of movement.^13-15^ According to the Fear Avoidance Model, people with chronic LBP presenting with higher levels of fear of movement are more probably to develop avoidance behaviour, leading to greater disability and lower physical activity levels.^16-18^ A recent meta-analysis showed that people with chronic LBP with high levels of disability are likely to present with lower levels of physical activity.^19^ Promoting a physically active lifestyle might therefore improve the psychosocial factors and reduce disability. Additionally, encouraging people to participate in physical activity has benefits beyond health, including social and economic benefits. The health benefits of physical activity in improving overall health status and reducing risk factors for non-communicable diseases are well documented.^20^

Walking is one of the simplest and preferred types of physical activity as it is functional, safe, accessible, cost-effective and does not require any special equipment.^21^ Despite the potential health benefits of walking, few studies have investigated its effectiveness in people with non-specific LBP. There is however conflicting results found in these studies. One trial^22^ found that a walking intervention was effective in decreasing disability and pain in participants with chronic LBP. But another trial^23^ reported a significant reduction in pain and disability in favor of other group with conventional physiotherapy and a group with medical exercise therapy compared to walking; this trial prescribed the walking intervention to participants as instructions and to be performed individually, and they were not supervised or monitored. However, the intensity and duration of walking were not measured, and the patient’s adherence to the treatment was not reported. Therefore, more high quality evidence on the effectiveness of walking for LBP is needed to guide prescription of walking as an intervention.

Lack of compliance is one of the challenges which may affect the success of walking programs.^24^ Poor compliance may be due to lack of individual motivation, goal setting, or inadequate program prescription. There is emerging evidence that physical activity interventions are more effective when they include technology that allows self-monitoring of target behaviour.^25, 26^ Current wearable accelerometers such as the Fitbit devices have features such as monitoring daily physical activity, providing feedback and motivating messages, and setting up goals. The wearable Fitbit devices have not only shown accuracy and validity in measuring step counts but have also shown potential to improve a person’s adherence and motivation.^27-29^ However, to the best of our knowledge no study has previously investigated the effect of the Fitbit device as a facilitator of a walking intervention in addition to usual care for the management of people with LBP.

**OBJECTIVES**

1. To examine the efficacy of Fitbit facilitated walking intervention in people with LBP with medium or high risk of chronicity in reducing disability and pain.

2. To examine the efficacy of Fitbit facilitated walking intervention in increasing physical activity levels in people with LBP.

**METHODS**

**Design**

The study design will be a randomised controlled trial. Participants will be randomised into two groups; Group 1/Experimental Group/Intervention Group: usual physiotherapy care plus Fitbit facilitated walking intervention and Group 2/Control Group: usual physiotherapy care alone. The study flowchart is displayed in **Figure 1**. This protocol was developed to adhere with the guidelines of the Standard Protocol Items: Recommendations for Interventional Trials (SPIRIT) and will be reported to comply with the 25-item Consolidated Standards of Reporting Trials(CONSORT) statement on trial reporting.^30^

Follow-up (week 26)

Participants with low back pain attending the physiotherapy clinic will be informed by the administrative staff about the study

Allocated to the experimental group (n=34)

Excluded

Inclusion criteria not met

Allocated to the control group (n= 34)

## Enrolment

Declines to participate

Screening: participants will be assessed for eligibility

Informed consent

Baseline data collection

Follow-up (week 26)

Post-intervention (week 9)

Post-intervention (week 9)

## Randomisation

## Post-intervention

## Follow-up

**Figure 1** Flow of participants through the trial.

**Eligibility criteria for participants**

Participants will be included in this study if they:

1. are diagnosed by physiotherapist with non-specific LBP;
2. are aged 18 years or over;
3. are categorized as being at medium or high risk of chronicity using STarT Back Screening Tool^31^;
4. are classified as physically inactive (those who engage in less than 150 minutes/week of moderate intensity, or less than 75 minutes/week of vigorous intensity or an equivalent combination of the two intensities of physical activity as determined by International Physical Activity Questionnaire (IPAQ)^32^;
5. are ready and able to participate in physical activity as determined by The Physical Activity Readiness Questionnaire (PAR-Q).^33^ Those deemed not fit to participate in physical activity by the PAR-Q or aged over 69 years, will need a clearance from their medical practitioner before engaging in physical activity;
6. have internet access.

Participants will be excluded if they have any:

1. contraindications to physical exercise (cardiovascular diseases e.g. myocardial infarction, embolism, or uncontrolled diabetes; orthopaedic impairments; balance problems);
2. serious spinal pathologies (e.g. fractures, tumours or inflammatory diseases such as ankylosing spondylitis);
3. neurological compromise (e.g. spinal nerve compromise or cauda equina syndrome);
4. pregnancy.

**Sample size**

A sample size was calculated using a similar method to that of a published study^34^ with a similar design which reported a mean post intervention disability score of 15.8 (SD=12.7) (measured by Oswestry LBP Disability Questionnaire) in the experimental group and 30.6 (SD=16.9) in the control group. The aim is to achieve 90% power to observe a significant difference of 5% (alpha of 0.05) using a two-tailed t-test. To allow for a 20% drop-out, the sample size was estimated to be 68 participants (34 participants in each group).

**Setting and recruitment**

Participants will be recruited from the physiotherapy outpatient departments of public and private hospitals or private physiotherapy practices in Sydney, Australia. Participants referred to the clinic will be informed about the study by the administrative staff who will also seek the approval of potential participants to pass their contact details to the associate investigator. Recruitment flyers will also be left in the waiting room or will be passed out by the staff to interested participants visiting the clinics. The investigator will contact participants via email and/or phone and provide more details about the study, check for the eligibility criteria and administer the surveys. A meeting will be arranged with the participating physiotherapists to explain the study protocol and agree on the research procedures.

**Enrolment**

Interested people with LBP will be assessed for eligibility to participate in the study by the therapist and investigator. Eligible people will receive information about the study protocol and written informed consent will be obtained. Also, the investigator will explain the protocol verbally and answer the participants’ questions before obtaining written informed consent. Participants who will sign the informed consent will be included in this study.

**Randomisation**

After confirmation of eligibility and signed informed consent is obtained, baseline outcome measurements will be collected (**Table 1**). After that, participants will be randomly allocated to one of the two groups. The randomisation process will be performed using computer-generated random numbers. The allocation sequence will be concealed from the investigator screening participants for inclusion and contained in sequentially, numbered, opaque and sealed envelopes. Usual physiotherapy care will be provided to participants by their treating physiotherapists who will determine the treatment pragmatically based on clinical reasoning. Participants may receive different treatment modalities depending on their physiotherapist and clinical presentation. Therefore, stratified block randomisation will be used to ensure fidelity and balance of the usual physiotherapy care given to participants in both groups at each participating clinic, and also to ensure equal sample sizes.

**Interventions**

**Control Group**

Participants allocated in the control group will receive usual physiotherapy care provided by their treating physiotherapist. Also, they will be given instructions to maintain their usual physical activity level during the treatment period.

**Experimental Group**

Participants in the experimental group will receive a Fitbit walking intervention provided by the investigators in addition to usual physiotherapy care provided by their treating physiotherapist.

During the baseline period, participants will be requested to wear a physical activity monitor (Axivity AX3 and Fitbit Flex wearable devices) for seven continuous days, to measure the total number of habitual walking steps per week. The baseline average daily walking steps for participants will be calculated by dividing the total number of habitual walking steps per week by seven (total walking steps per week/7). During the intervention each participant’s average daily walking steps will be progressed each week by a minimum 10%. To comply with current physical activity guidelines, participants will be asked to walk the prescribed number of steps at a moderate intensity (i.e. brisk walking, 100 step/min).^35-38^ Participants will be asked to partake in the prescribed walking program at least five days per week for 8 weeks.

Participants in the experimental group will receive a Fitbit Flex wearable device and will attend a training session delivered by the investigator to: 1) install and set up the Fitbit wearable device and account, 2) register the participant in the 10,000 Steps website and synchronise the device with the Fitbit account, and 3) provided with instructions of using the device and account including monitoring step counts as well as other features. Additionally, participants will receive a handbook detailing all of the instructions provided from the training session.

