**“Fitbit Facilitated Walking Intervention” conceptual basis and development:**

The Fitbit facilitated walking intervention was developed for patients with LBP, using physical activity guidelines^39, 40^ in order to assist them maintain their usual activities, and to improve their compliance with the prescribed therapeutic exercise. The intervention consists of: 1) Fitbit wearable device, 2) 10,000 Steps website, and 3) progressive walking program.

The Fitbit device will enable participants to monitor their progress in meeting the target number of steps. Further, the Fitbit wearable device will act as a motivational feedback tool providing immediate information on activity levels. The 10,000 Steps website is a non-profit promotion web-based platform that was developed to increase the physical activity level of the general community and it can be connected and synchronised with the Fitbit account. We are using this website to encourage participants to use the Fitbit device, track and monitor the daily steps progress and share it with other participants. Also, it enables the investigator to monitor and track the participants’ progress and keep in contact with them. The website has high levels of usability.^41^

The average steps inactive people walk (for any purpose) is less than 5000 steps per day.^35, 36^ Therefore, for people to adhere to PA guidelines, they need to start a graded walking program which will be progressed by at least 10% each week.

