**Fitbit Flex wearable device**

The physical activity level and average number of walking steps per day for participants in the experimental group will be measured by Fitbit Flex wearable device.^43^ The Fitbit Flex is a wristband activity monitor that contains a tri-axial accelerometer. The data can be uploaded to the Fitbit website which will be synchronized with 10,000 Steps website. This device has been shown to be accurate and valid in measuring physical activity and quantifying steps.^27, 28, 44^

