**Secondary outcomes**

**Habitual physical activity level and walking steps**

Habitual physical activity level and walking steps in both groups will be measured objectively by Axivity AX3 (Newcastle upon Tyne, UK; product website: http://axivity.com/product/ax3) for seven continuous days. The Axivity AX3 is a wristband activity monitor that contains a tri-axial accelerometer. The device is waterproof, small, light and is ideal for collecting longitudinal movement data. This device has been shown to be accurate and valid in measuring walking steps.^49-51^

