**Data collection and management**

The subjective data (disability, pain, depression, fear of movement and pain catastrophising) will be collected online using Research Electronic Data Capture (REDCap).^63^ The objective data (habitual physical activity level and daily walking steps) will be collected by Axivity AX3**.**

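### The protocol has the Fitbit worn in the baseline week by the experimental group, but baseline precedes allocation, so the baseline for the step and activity outcomes may not be habitual

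*Protocol*

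**What the plan says.** On sequence, the Randomisation section is clear. Once eligibility is confirmed and "signed informed consent is obtained, baseline outcome measurements will be collected", the Table 1 measures are taken. "After that, participants will be randomly allocated to one of the two groups". The flow in Figure 1 has the same order. Table 1 includes habitual activity and daily steps by Axivity AX3, so the baseline for those outcomes is meant to be a pre-randomisation measurement.

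On the outcome device, the protocol is also consistent. "Habitual physical activity level and walking steps in both groups will be measured objectively by Axivity AX3", and the Data collection and management section repeats it: "The objective data (habitual physical activity level and daily walking steps) will be collected by Axivity AX3".

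The difficulty is in the Experimental Group section. For the baseline period it says that "participants will be requested to wear a physical activity monitor (Axivity AX3 and Fitbit Flex wearable devices) for seven continuous days". The section headed Fitbit Flex wearable device ties that device to one arm: "average number of walking steps per day for participants in the experimental group will be measured by Fitbit Flex wearable device". The Control Group section mentions no Fitbit. The section on the conceptual basis of the intervention lists the Fitbit as the first of its three components and says that "the Fitbit wearable device will act as a motivational feedback tool providing immediate information on activity levels".

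The weekly total from that baseline week is turned into a daily average ("total walking steps per week/7"), from which the walking programme progresses. The text names two devices and one total, without saying which device supplies it.

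**The concern.** A week of monitoring that comes before allocation cannot be arranged for one arm. Read together, these sections leave open who wears the Fitbit at baseline and whether that week falls before or after the envelope is opened.

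This matters because the Fitbit is part of the treatment under test and is meant to change walking. If it is worn beside the AX3 and does change walking, the AX3 records the changed walking. Using the same outcome instrument in both arms does not prevent that. At stake is the baseline for objective 2, the effect on physical activity level. The primary outcomes, disability and pain, do not use this measurement.

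**Working it through.** The plan states no figure to reproduce here. The check sets the sections side by side and then sizes the consequence under stated assumptions.

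**Possible readings**

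1. The experimental arm wears AX3 plus Fitbit for a week after allocation, and controls wear the AX3 alone. This fits the Experimental Group, Control Group and Fitbit Flex sections, but contradicts the Randomisation section and Figure 1. The experimental baseline is then a post-randomisation measurement.
2. Everyone wears AX3 plus Fitbit before allocation. This fits the Randomisation section, but the other three sections are then incomplete, and controls are exposed to a listed intervention component.
3. Only future experimental participants wear the Fitbit before allocation. This is impossible, because the allocation sequence is concealed.

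**Inputs for size**

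- Illustrative habitual level: 5,000 steps a day. The protocol gives this as the level below which inactive people walk on average.
- Minimum weekly progression: 10% (Experimental Group section).
- Rise in walking caused by visible feedback in the baseline week: r = 5% to 20%. This is an assumption; the protocol gives no figure.

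**Overstatement of baseline:** δ = r × 5,000.

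- r = 5%: 0.05 × 5,000 = 250 steps a day.
- r = 20%: 0.20 × 5,000 = 1,000 steps a day.

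For scale, two weeks of minimum progression take 5,000 to 5,000 × 1.1 × 1.1 = 6,050. The upper case, 5,000 × 1.2 = 6,000, is therefore about two weeks of the programme.

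**Shift in the between-arm estimate (experimental minus control)**

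| Analysis of steps | Reading 1 | Reading 2 |
|---|---|---|
| Change from baseline | −δ = −250 to −1,000 | −δ − (−δ) = 0 |
| Adjusted for baseline, slope β between 0 and 1 | −βδ, between 0 and the line above | 0 |
| Follow-up value only | 0 | 0 |

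The reading 2 column assumes that the Fitbit affects both arms equally in that week, as randomisation would give on average, and that its wear leaves no later effect in controls. Each arm's own change would still be understated by δ, because the starting value is not habitual. Under reading 1 the shift works against the intervention: an inflated experimental baseline makes that arm's gain look smaller.

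**The case against.** The strongest reply is that the outcome is well protected. Steps and activity are measured by the AX3 in both groups at all three time points, so the instrument is common. The sentence on baseline wear says only that participants wear both devices; the restriction to one arm comes from its heading and from the Fitbit Flex section. Device set-up, website registration and instruction in monitoring steps take place at a training session described later in the Experimental Group section, and the investigator's weekly feedback belongs to the treatment period. The Fitbit might therefore be worn at baseline with no feedback in use. The Statistical analysis section names generalized linear models without committing to change scores or baseline adjustment, so any bias depends on an analysis choice not made here.

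Much of this stands. A reader might infer that the two arms' baselines are simply not comparable, or that the outcome baseline is taken from the Fitbit in one arm. The documents support neither. The outcome device is the AX3 throughout, and a difference between arms arises under only one of the two workable readings, and only if feedback is visible.

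A reader might also infer that the fixed divisor of seven spoils the baseline when wear is incomplete. That does not hold as a finding. Seven days of wear are requested, and for seven days the division is exact. The divisor does not by itself separate the arms, and a valid-day rule for the outcome may properly sit in an analysis plan that is not shown.

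What the reply does not remove is the contradiction of sequence. No section says whether feedback is hidden in the baseline week, and a common instrument does not help if the behaviour it records has been altered.

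**Conclusion.** The point holds as an internal contradiction with a conditional consequence. The protocol places the AX3 baseline before allocation, yet describes wearing the Fitbit in that same week as something the experimental group does. Unless feedback is hidden, the baseline for objective 2 may not be habitual. If the week follows allocation in one arm, the baseline may also differ between arms.

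On an assumed 5 to 20% reaction and a 5,000-step level, the first reading understates the experimental arm's gain by 250 to 1,000 steps a day in a change-based analysis, by part of that in a baseline-adjusted one, and not at all in a comparison of follow-up values. Under the second reading the between-arm contrast is preserved on the assumptions above, but controls have worn an intervention component. The primary outcomes are untouched. The change is worth making because it is cheap and secures a named objective; the contradiction does not threaten the trial's main conclusion.

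**What to change.** In the Randomisation, Experimental Group and Fitbit Flex wearable device sections, state that:

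- all participants wear the AX3 only, for seven days, before the envelope is opened;
- that week is the baseline for the step and activity outcomes in both arms;
- the Fitbit is issued only after allocation, to the experimental arm, and any Fitbit calibration data stay out of the outcome baseline.

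Separately, reconcile the Experimental Group section on which device supplies the weekly total that starts the walking progression. That is for the investigators to settle; no target rule is proposed here.

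The cost is rewording of three sections and issuing the Fitbit about a week later. No new equipment is needed, since the AX3 is already used in both groups at baseline.
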